### Recruitment {15}

Participants will be recruited from Nanjing Drum Tower Hospital (Nanjing, China), a certified center for PGT. Recruitment efforts will involve multiple channels, including online announcements, hospital bulletin boards, and posters. A dedicated telephone line will be available for interested individuals to obtain additional information. Eligible candidates visiting the outpatient clinic will be invited to have an in-person discussion with study staff, during which comprehensive details about the trial will be provided. Patients who meet the inclusion criteria and express willingness to participate will be asked to sign a written informed consent form. The recruitment period is scheduled from December 2022 to December 2025, with an expected enrollment rate exceeding 95%.

## Assignment of interventions: allocation

### Sequence generation {16a}

All oocytes retrieved in each cycle will be evenly distributed into two fertilization dishes (Dish 1 and Dish 2). If an odd number of oocytes is retrieved, the extra oocyte will be placed in Dish 1. The randomization will be performed using SAS 9.4 statistical software, applying a completely randomized method.

### Concealment mechanism {16b}

The use of SAS to randomize using a password-restricted website will ensure concealment.

### Implementation {16c}

A research assistant independent from analysis generates the sequence and prepares dish labels.

## Assignment of interventions: blinding

### Who will be blinded {17a}

This study is an open trial. Both patients and researchers know the group assignments in the trial, and only the statisticians are blinded to the grouping.

### Procedure for unblinding if needed {17b}

No procedures are needed for unblinding until the finalization of the main data analysis.

## Data collection and management

### Plans for assessment and collection of outcomes {18a}

All clinical and laboratory data will be collected by trained staff using standardized forms. Intervention will be performed by experienced laboratory personnel using uniform criteria. To ensure data quality, double data entry and periodic cross-checks will be conducted. All data collection instruments have been validated internally and reviewed by the study monitoring team. Data collection forms will be stored electronically in a secured database and can be provided upon request or found in the supplementary materials.

### Plans to promote participant retention and complete follow-up {18b}

To enhance participant retention and ensure complete follow-up, all participants will receive regular reminders via phone or text messages. A dedicated study coordinator will be available to address participant concerns and facilitate scheduling of follow-up visits. Financial incentives, such as reduced PGT-A testing fees, will also be provided. Based on our experience, participants are usually grateful for any research conducted due to the strong reproductive requirements.

### Data management {19}

All clinical and laboratory data will be entered into a password-protected electronic data capture system by two independent research assistants to ensure accuracy (double data entry). Each participant will be assigned a unique study ID to ensure de-identification. Range checks, logical consistency checks, and regular audits will be performed to maintain data quality. All data will be stored on a secure hospital server with restricted access granted only to authorized study personnel. Backups will be scheduled weekly. Data will be encrypted both in transit and at rest.

### Confidentiality {27}

All personal information from potential and enrolled participants will be collected through secure hospital systems and documented using standardized case report forms. Each participant will be assigned a unique study identification code, and identifiable information will be stored separately from clinical data. Only authorized members of the research team will have access to identifiable information. All electronic data will be stored on password-protected, encrypted servers within the hospital’s network. Paper-based records, if any, will be kept in locked filing cabinets in restricted-access areas.

Throughout the trial and after its conclusion, all data will be handled in accordance with applicable data protection regulations. Identifiable data will not be shared outside the research team. Upon study completion, personal identifiers will be removed or anonymized before data archiving or analysis.

### Plans for collection, laboratory evaluation, and storage of biological specimens for genetic or molecular analysis in this trial/future use {33}

Trophectoderm biopsy samples collected during PGT-A will be used solely for chromosomal screening as part of the clinical protocol. No additional biological specimens will be collected for genetic or molecular studies. Biopsied cells will be analyzed using next-generation sequencing in a certified clinical laboratory. No biological samples will be stored for future use in ancillary studies. Participants will be informed accordingly, and no additional consent for biobanking is required.

## Statistical methods

### Statistical methods for primary and secondary outcomes {20a}

Data analysis will be conducted using SPSS version 13.0. Descriptive statistics will summarize baseline demographic and clinical characteristics. Categorical variables—including clinical pregnancy rate, implantation rate, and miscarriage rate—will be compared between groups using the chi-square (*χ*^2^) test or Fisher’s exact test where appropriate. Continuous variables such as patient age, baseline FSH levels, antral follicle count (AFC), total gonadotropin dosage and duration, number of oocytes retrieved, and fertilization rate will be analyzed using independent-samples *t*-tests or nonparametric equivalents as appropriate. To account for potential confounding factors, multivariable regression analyses will be conducted. Logistic regression models will be applied for binary outcomes (e.g., clinical pregnancy, implantation, miscarriage), while linear regression will be used for continuous outcomes (e.g., number of mature oocytes, fertilization rate). Models will adjust for maternal age, baseline FSH levels, AFC, ovarian stimulation parameters, and other relevant covariates. For pregnancy outcomes, paternal factors such as age and semen parameters will also be included as covariates. A two-sided *p*-value < 0.05 will be considered statistically significant. Effect sizes will be reported with 95% confidence intervals. Sensitivity analyses will be conducted to test the robustness of the results.

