### Trial design {8}

This is a single-center, prospective, randomized, within-subject controlled superiority trial with a theoretical 1:1 allocation of cumulus-oocyte complexes (COCs) to intervention vs. control.

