## Interventions

### Explanation for the choice of comparators {6b}

The standard control will consist of oocytes from the same individual that were cultured under routine IVF/ICSI laboratory conditions without MVA supplementation. This comparator represents the current standard of care in IVF/ICSI laboratory practice and allows for a direct evaluation of the effect of MVA treatment under otherwise identical conditions. By randomly allocating oocytes from the same patient into intervention and standard control groups, the design minimizes inter-individual variability and thereby enhances the internal validity of the study.

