### Intervention description {11a}

A total of 150 PGT-A cycles will be included in the study. All retrieved COCs from each cycle will be randomly allocated into two parallel groups: the MVA supplementation group (intervention group) and the standard control group. Randomization will be performed at the level of sibling oocytes to minimize inter-individual variability.

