## Discussion

AMA is strongly associated with oocyte aneuploidy, which remains a major cause of implantation failure, miscarriage, and reduced live birth rates. Emerging evidence has highlighted the MVA pathway as a key regulator of oocyte meiotic maturation and genomic stability. Previous studies demonstrated that disruption of this pathway in granulosa cells is associated with impaired LHR and EGF signaling, leading to defective meiosis and increased aneuploidy [8]. In animal models, supplementation with MVA metabolites has been shown to mitigate meiotic errors, restore proper chromosome segregation, and reduce aneuploidy rates in aging oocytes [8]. These preclinical findings suggest that maintenance of MVA pathway integrity is critical for safeguarding oocyte quality during reproductive aging. Building on this evidence, the present study represents the first randomized controlled trial (RCT) to evaluate MVA supplementation in human-assisted reproduction. By directly translating preclinical discoveries into a clinical setting, this trial seeks to test whether short-term MVA supplementation during the pre-fertilization stage can enhance oocyte competence and increase the yield of euploid embryos in women of AMA.

A RCT was selected as the study design as it represents the gold standard for clinical research, effectively minimizing bias and providing the highest level of evidence for causal inference. A within-subject controlled approach was further adopted, whereby COCs from the same stimulation cycle are randomly allocated to MVA-supplemented or standard fertilization medium. This strategy maximizes statistical efficiency by controlling for inter-individual variability and thereby enhances the ability to detect the true effect of MVA supplementation. Women aged 38–42 years were specifically targeted as younger patients show low baseline aneuploidy, while women above 42 typically yield insufficient oocytes for analysis. This choice is also consistent with clinical practice guidelines, which recommend considering preimplantation genetic screening in women over 38 years [9]. The intervention parameters (50 µM for 4 h before insemination) were chosen based on effective conditions in animal studies and are readily integrated into routine IVF/ICSI practice.

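### The tests named in {20a} assume two independent groups, but each cycle's sibling oocytes are split between both arms

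*Protocol article*

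**What the plan says.** Several sections fix a split within the woman. Trial design {8} specifies a "randomized, within-subject controlled superiority trial with a theoretical 1:1 allocation of cumulus-oocyte complexes (COCs) to intervention vs. control". The comparator section {6b} states: "The standard control will consist of oocytes from the same individual". The intervention description {11a} adds: "Randomization will be performed at the level of sibling oocytes to minimize inter-individual variability". Sequence generation {16a} divides each cycle's oocytes evenly over two dishes. The Discussion gives the reason: "This strategy maximizes statistical efficiency by controlling for inter-individual variability".

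Statistical methods {20a}, whose heading covers primary and secondary outcomes, reads as a parallel-group plan. Categorical variables "will be compared between groups using the chi-square" or Fisher's exact test. Continuous variables, among them age, FSH, antral follicle count, gonadotropin dose and fertilization rate, "will be analyzed using independent-samples" t-tests or nonparametric equivalents. Logistic and linear regressions adjust for age, FSH, antral follicle count and stimulation parameters. The section names no paired, stratified, conditional, GEE or mixed-model analysis. It does not mention the euploid rate by name.

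**The concern.** A chi-square or independent-samples t-test takes the two arms to be unrelated sets of observations. Here the arms consist of siblings from the same women, and oocytes within an arm share a woman and a dish. Some women also contribute more than one cycle, since 128 women give about 150 cycles. The efficiency claimed in the Discussion exists only if the analysis uses the pairing.

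Two kinds of correlation pull in opposite directions. A shared woman effect cancels in the within-woman difference, so the chi-square standard error is too large. A shared dish effect (medium, handling) does not cancel, so the chi-square standard error is too small. The net direction is not known beforehand, and it bears on the primary test at two-sided 0.05.

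The covariate plan has the same flaw. In the laboratory comparison, a woman with oocytes in both dishes has the same age, FSH, follicle count and gonadotropin dose in both arms. A between-arm test of these values compares a set of women with itself, and adjusting for them does not replace a woman or cycle term.

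**Working it through.** **Inputs.** From Sample size {14}: 10% versus 17% euploid per mature oocyte, alpha 0.05, 371 then 408 mature oocytes per group, 5.45 mature oocytes per cycle, about 150 cycles. From the Abstract: 128 women. Assumed: 80% power (none is stated) and all correlations.

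**1. The plan's own figure.** The formula for two independent proportions with unpooled variance gives

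(1.960 + 0.842)² × (0.10×0.90 + 0.17×0.83) / 0.07² = 7.849 × 0.2311 / 0.0049 = 370.2, so 371 per group.

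Then 371 × 1.10 = 408.1, and 2 × 408 / 5.45 = 149.7 cycles. The plan's numbers are reproduced, so the sample size also treats oocytes as independent.

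**2. Standard error used by chi-square.** At 10% in both arms: √(2 × 0.10 × 0.90 / 408) = 0.0210.

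**3. True standard error.** Let ρ be the correlation between any two oocytes of a woman, δ the extra correlation within a dish, and m = 5.45/2 = 2.725 mature oocytes per dish. Each arm's variance is multiplied by 1 + (m−1)(ρ+δ), and the covariance between arms removes mρ. The net factor is

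F = 1 − ρ + (m−1)δ = 1 − ρ + 1.725δ.

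- Woman effect only, ρ = 0.08: F = 0.92, √F = 0.959. The chi-square SE is too large.
- Woman 0.03, dish 0.05: F = 1.056, √F = 1.028. Woman 0.06, dish 0.09: F = 1.095, √F = 1.047. The chi-square SE is about 3 to 4% too small with equal dishes, and more with uneven yields.
- Break-even: δ = ρ/1.725 ≈ 0.58ρ.

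**4. Simulation.** 150 cycles, 1 + Poisson(4.45) mature oocytes per cycle, even split with the odd oocyte falling to either arm at random, probit random effects, each cycle treated as its own cluster. There were 20,000 runs at 10% versus 10% and 10,000 at 10% versus 17%. Without a dish effect, latent woman variances of 0.1, 0.2, 0.3 and 0.5 correspond to ρ of about 0.04, 0.08, 0.13 and 0.25.

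| Latent variance woman / dish | Type I, chi-square | Type I, clustered | True SE | Chi-square SE | Power, chi-square | Power, clustered |
|---|---|---|---|---|---|---|
| 0 / 0 | 5.08% | 5.34% | 0.0210 | 0.0210 | 83.7% | 83.9% |
| 0.1 / 0 | 4.54% | 5.20% | 0.0206 | 0.0210 | 84.1% | 84.8% |
| 0.2 / 0 | 4.03% | 5.31% | 0.0203 | 0.0210 | 84.6% | 86.5% |
| 0.3 / 0 | 3.56% | 5.15% | 0.0197 | 0.0210 | 85.1% | 87.7% |
| 0.5 / 0 | 2.67% | 5.13% | 0.0185 | 0.0209 | 87.1% | 91.6% |
| 0.1 / 0.1 | 6.05% | 5.47% | 0.0218 | 0.0209 | 83.0% | 81.5% |
| 0.2 / 0.2 | 7.20% | 5.35% | 0.0227 | 0.0209 | 81.8% | 77.9% |
| 0.1 / 0.3 | 8.38% | 5.14% | 0.0239 | 0.0209 | 81.2% | 74.1% |

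In the last three rows the higher chi-square power is not a gain, because that test exceeds its nominal level.

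**5. Repeat with women as clusters.** 128 women, 22 of them with a second cycle (150 − 128), negative-binomial yields, null rate 13.5%, 4,000 runs per scenario. With woman-level ICC 0.11 to 0.21, chi-square type I error is about 4% to 3%. Power is 85.3% against 86.7% for the woman-clustered test at the lower ICC, and 86.4% against 89.9% at the higher. With total ICC 0.08 to 0.15, of which 0.03 to 0.06 is woman-level, chi-square type I error is about 7 to 8% and its SE is 8 to 13% too small.

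**The case against.** **The primary outcome is not in the quoted sentence.** Its examples are pregnancy outcomes, which are defined per patient or per pregnancy, and an analysis plan that is not shown could hold the primary model. The first part is true. But the section is headed as covering the primary outcome, the list of examples is open, no other method is offered, and the sample size uses the same independence assumption. Fertilization rate, a laboratory outcome comparing sibling oocytes, is explicitly given an independent-samples test. This is a stated method that does not fit the design, not an omitted detail.

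**A conservative test does not produce false positives.** This stands for the woman-only case: the cost there is wider intervals and lost power.

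**The inflation depends on an assumed dish correlation.** This also stands. The article requires identical laboratory conditions in both arms and presents differences between women as the variation to control. In a further simulation with woman ICC about 0.07 to 0.10 and dish part about 0.02 to 0.04, chi-square type I error was 4.5 to 6.0% and the SE was within about 3%. The larger errors arose where the dish part equalled or exceeded the woman part. The 8 to 13% SE error also needs uneven yields.

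**Baseline comparisons could be meant for women grouped by the arm of the transferred embryo.** For pregnancy outcomes that is possible, and covariate adjustment there is not criticised. The Abstract's wording that women are randomized to one group or the other may explain the parallel-group template, but it conflicts with the sections of the body that define the allocation.

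**Conclusion.** The concern holds. The mismatch between the within-woman design and the independent-groups analysis is certain from the text. Its numerical effect is not, because the documents give no intra-woman or intra-dish correlation.

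Over the assumed ranges, the chi-square SE runs from about 13% too large (0.0209 against 0.0185) to about 13% too small (0.0209 against 0.0239), with type I error between 2.7% and 8.4%. It is correct only if sibling oocytes are uncorrelated or the two components happen to cancel. Inflation should not be presumed: with a dominant woman effect the harm is lost efficiency. Because the direction is unknown and the primary test is affected, this should be corrected before the analysis is run.

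**What to change.** Rewrite {20a} for the laboratory outcomes:

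- **Primary analysis.** An oocyte-level logistic mixed model with arm as fixed effect and random intercepts for woman and cycle/dish, or a GEE, with standard errors clustered by woman. Choose one in advance. With two to three mature oocytes per dish and 10 to 17% events, a dish intercept is weakly identified, which favours the GEE. A Cochran-Mantel-Haenszel test stratified by cycle or conditional logistic regression would use the pairing but would not cover dish correlation.
- **Estimate.** Report the marginal risk difference with its 95% confidence interval.
- **Other laboratory outcomes.** Use the same structure for fertilization and blastocyst rates.
- **Baseline.** Describe the women once. Delete between-arm baseline tests and woman-level confounder adjustment for laboratory outcomes.
- **Consistency.** Bring the Abstract's description of randomization into line with the oocyte-level split, and restate the sample size with its assumed correlations.

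The cost is wording and a few lines of code. SAS 9.4, already named for randomization, can fit these models. No patients or data are added. The last biopsy was in January 2025 and the article requires ethics approval before analysis methods change, so this must be a dated amendment, made while the statisticians are still blinded.

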### Sample size {14}

Among women of AMA (38 ≤ age ≤ 42 years) undergoing treatment at this center, the current euploid blastocyst rate (defined as the number of euploid blastocysts per mature oocyte retrieved) is approximately 10%. This study is designed to increase this euploid rate to 17% with a significance level (α) of 0.05. To achieve this, each group is expected to include 371 mature oocytes, accounting for an estimated 10% dropout rate. This results in a final target of 408 mature oocytes per group. Given the average mature oocyte yield per cycle in women aged 38–42 years is approximately 5.45 oocytes, the study anticipates enrolling approximately 150 cycles in total.

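### Mature-oocyte counts and fertilization rates are sent to linear regression and t-tests without a denominator or weight, in a split-dish design with about 2.7 mature oocytes per dish (supportive laboratory measures; minor)

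*Protocol article*

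**What the plan says.** Three places in the protocol article bear on this.

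- **Statistical methods {20a}.** For adjusted analyses, "linear regression will be used for continuous outcomes (e.g., number of mature oocytes, fertilization rate"). For unadjusted comparisons, "number of oocytes retrieved, and fertilization rate will be analyzed using independent-samples *t*-tests or nonparametric equivalents as appropriate". On covariates: "Models will adjust for maternal age, baseline FSH levels, AFC, ovarian stimulation parameters, and other relevant covariates". The number of COCs placed in a dish is not among those named.
- **Sequence generation {16a}.** COCs are divided evenly between two dishes. "If an odd number of oocytes is retrieved, the extra oocyte will be placed in Dish 1". Then: "The randomization will be performed using SAS 9.4 statistical software, applying a completely randomized method". The text does not say whether the draw decides which dish receives mevalonate (MVA) or whether Dish 1 always belongs to the same arm. Trial design {8} calls the ratio a "theoretical 1:1 allocation of cumulus-oocyte complexes (COCs) to intervention vs. control".
- **Sample size {14}.** The "average mature oocyte yield per cycle in women aged 38–42 years is approximately 5.45 oocytes", with about 150 cycles planned.

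The primary outcome in {12}, euploid embryos per mature oocyte, has its own denominator and is not named in the regression sentence. The secondary outcomes in {12} are clinical pregnancy, miscarriage and live birth.

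**The concern.** A comparison by arm needs a unit of analysis. In this design the natural unit that has a fertilization rate within one arm is the dish. Ordinary linear regression or a t-test then gives each dish the same weight, whether it holds one mature oocyte or six. A dish with no mature oocyte has no rate per mature oocyte and drops out after allocation. With fewer than three mature oocytes per dish on average, neither effect is negligible.

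The number of mature oocytes raises a different problem. It cannot exceed the number of COCs put in the dish, and {16a} sets that number by rule. A raw count therefore reflects dish size as well as maturation. Age, FSH, AFC and stimulation parameters are identical for both dishes of a cycle, so adjusting for them cannot remove a difference in dish size.

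What is at stake is how the supportive laboratory results are read. The rationale is that the MVA pathway supports oocyte maturation, so a difference in mature oocytes would be taken as biology. Mature oocytes are also the denominator of the primary outcome, so whether that denominator differs by arm is a useful check that deserves a sound method.

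**Working it through.** **1. The plan's own figures.** For 10% versus 17%, two-sided 0.05, with 80% power assumed (the article states none) and unpooled variance: n = (1.960 + 0.842)² × (0.10×0.90 + 0.17×0.83) / 0.07² = 370.2, so 371 per group, as stated. 371 × 1.1 = 408. Cycles: 2 × 408 / 5.45 = 149.7, about 150. Mature oocytes per dish: 5.45 / 2 = 2.725.

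**2. Assumptions not in the article.** Share of COCs that are mature, m = 0.75–0.85. COCs per cycle have mean 5.45/m and follow a Poisson or a more spread negative binomial distribution (k = 3). Per-oocyte success is 0.7 or 0.1, with intra-cycle correlation 0–0.3. Under these settings 50–53% of cycles have an odd number of COCs.

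**3. Fertilization rate, equal weights.** With n mature oocytes in a dish and no heterogeneity between dishes, the variance of the unweighted mean of dish rates relative to the pooled rate is E[n] × E[1/n] over dishes with n > 0. As an illustration, take one dish with 1 and one with 6: 3.5 × (1 + 1/6)/2 = 2.04. Over the assumed distribution of dish sizes, the formula gives 1.26–1.28 (Poisson) and about 1.48 (negative binomial). Simulation of 150 cycles without an MVA effect, with correlation 0–0.3, gives 1.14–1.53 against pooled or within-cycle Mantel–Haenszel estimates. That is roughly 15–50% more variance.

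In the simulations about 1–13% of dishes had no mature oocyte. The bias of the rates was at most 0.003 in absolute value, within simulation error, whether or not Dish 1 was tied to an arm.

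**4. Mature-oocyte count, Dish 1 drawn per cycle.** The expected difference is 0. Per cycle, the variance of the difference in counts has two parts:
- from maturation: m(1−m) × 5.45/m = (1−m) × 5.45;
- from the odd COC: m² × P(odd).

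The relative excess due to dish size is m² × P(odd) / [(1−m) × 5.45]. With P(odd) = 0.50:
- m = 0.75: 0.281 / 1.363 = 0.21
- m = 0.85: 0.361 / 0.818 = 0.44

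Simulation over the wider settings gives about 16–49%. No false positives result: the independent t-test rejects in under 1% of null trials, because it ignores pairing, and a paired test in 4–7%.

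**5. Mature-oocyte count, Dish 1 always one arm.** The spurious difference per cycle is m × P(odd): 0.75 × 0.50 = 0.375 up to 0.85 × 0.53 = 0.45. That is about 14–16% of a dish. On this premise alone, null trials are falsely significant in 24–96% of cases with the independent t-test, depending heavily on the spread of yields, and in 96–100% with a paired test.

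**The case against.** A reader might infer from {16a} that the extra COC in Dish 1 contaminates the MVA comparison outright, and quote the high false-positive rates in step 5. The article does not support that. Nowhere does it tie Dish 1 to one arm. {16a} describes the split into dishes and then a randomization, and {16c} has an independent assistant produce the sequence and the dish labels. This fits a draw that decides which dish receives MVA, in which case the odd COC adds noise and no bias. Even under the unfavourable mapping, only raw counts are biased. Fertilization rates and the primary endpoint are not.

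Other objections carry weight:
- These measures are not in {12}. The number of mature oocytes appears only as an example for the regression.
- Per-dish values and equal weights are not the article's words. They are the ordinary consequence of the stated tests.
- The number of oocytes retrieved is listed beside age, FSH and AFC. It reads as a description of the cycle, so no fault is found with it here.
- Maturity, spread of yields and correlation are assumed, so only ranges can be given.

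It can also be said that denominators for supportive measures belong in a statistical analysis plan. That would answer silence, but {20a} names the methods. A later plan would have to replace them. The open reference to further covariates and sensitivity analyses does not supply a denominator.

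**Conclusion.** The point holds as a minor one. The stated methods for two supportive laboratory measures ignore denominators that are known for every dish. For fertilization rate the cost is precision (about 15–50% more variance) and the loss of about 1–13% of dishes, without bias from the split rule. For mature-oocyte counts the cost is about 16–49% extra variance if the arm of Dish 1 was drawn per cycle, and a spurious difference of about 0.4 per cycle if it was not. The article leaves open which of these applies, and its wording on dish labels makes the second less likely. All sizes rest on assumed maturity of 75–85% and on the assumed spread of COC numbers.

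**What to change.** In {20a}, replace linear regression and t-tests for these two measures with binomial models that carry the dish denominators and account for the cycle (for example a random cycle effect, or a comparison stratified by cycle):

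- **maturation:** mature oocytes / COCs allocated to the dish;
- **fertilization:** fertilized / COCs allocated, which keeps dishes with no mature oocyte, so that only a cycle with a single COC leaves a dish without a denominator. Fertilized per mature oocyte can be reported as supportive.

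In {16a}, state how dish number mapped to arm. If Dish 1 was always the same arm, raw counts should not be compared between arms at all.

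The cost is a few sentences of analysis text and no new data, since COCs per dish are fixed at allocation. The team should confirm that the software named in {20a} can fit the chosen model. According to the trial status section, the last embryo biopsy was in January 2025 and the manuscript was submitted before the end of data analysis. Changing the allocation rule would therefore no longer help, but the analysis could still be changed then. Any change should be dated and fixed before the arms are compared.

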***Exclusion criteria***
Egg donation cycleKnown parental chromosomal abnormalitiesUterine disorders likely to impair implantation, including adenomyosis, uterine fibroids, uterine malformations, thin endometrium (< 7 mm), or endometriosis;History of recurrent implantation failure (≥ 3 failed embryo transfers with good-quality embryos)Severe systemic illness or uncontrolled endocrine/metabolic disease that may affect ovarian function (e.g., uncontrolled diabetes, thyroid dysfunction, or hyperprolactinemia)

Male partner eligibility is not restricted beyond a requirement for normal semen analysis; no additional exclusion criteria are applied to male partners. No restrictions are placed on study personnel or the participating center.

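### The adjusted logistic model for miscarriage has at least nine slopes for perhaps 2 to 12 events, so at the lower counts it often has no finite estimate

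*Protocol article*

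**What the plan says.** Everything at issue is in the article's section on statistical methods for primary and secondary outcomes {20a}. It first plans chi-square or Fisher tests for pregnancy, implantation and miscarriage. It then adds regression: "Logistic regression models will be applied for binary outcomes (e.g., clinical pregnancy, implantation, miscarriage"). The common adjustment set is stated as: "Models will adjust for maternal age, baseline FSH levels, AFC, ovarian stimulation parameters, and other relevant covariates". A further set follows: "For pregnancy outcomes, paternal factors such as age and semen parameters will also be included as covariates". The section also promises effect sizes with 95% confidence intervals, and "A two-sided *p*-value < 0.05 will be considered statistically significant". It does not say which test of the group coefficient is meant.

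Two other sections bear on how many events there will be. The outcomes section {12} divides clinical pregnancies by patients with a transfer, and miscarriages by clinical pregnancies. The sample size section {14} starts from a euploid rate of about 10% per mature oocyte, and "This study is designed to increase this euploid rate to 17% with a significance level (α) of 0.05". It converts oocytes to cycles as follows: "Given the average mature oocyte yield per cycle in women aged 38–42 years is approximately 5.45 oocytes".

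**The concern.** A logistic model needs enough events for the number of coefficients it carries. Miscarriage sits at the end of a chain: a cycle must yield a euploid blastocyst, the woman must have a transfer, she must become pregnant, and the pregnancy must then be lost. Each step shrinks the numbers, while the covariate list is longest for exactly these outcomes.

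When events are few relative to slopes, some combination of covariates often separates miscarriages from ongoing pregnancies perfectly. The maximum-likelihood estimate is then infinite and the promised odds ratio with its 95% interval cannot be given. Where a finite estimate exists, its p-value need not hold the nominal level. The trial would have committed itself to an adjusted miscarriage result that it may be unable to produce, or that cannot be read at face value.

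**Working it through.** **1. The plan's own figures.** For 10% versus 17%, two-sided α = 0.05 and 80% power (power is not stated; 80% is assumed because it reproduces the figure), the unpooled formula gives (1.96 + 0.842)² × (0.10×0.90 + 0.17×0.83) / 0.07² = 7.849 × 0.2311 / 0.0049 ≈ 370.2, so 371 per group. Then 371 × 1.10 ≈ 408, and 2 × 408 / 5.45 = 149.7, so 150 cycles. The sample size section reproduces.

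**2. Slopes in the miscarriage model.** Maternal age, FSH and AFC make 3. Stimulation parameters are plural, and the same section names gonadotropin dose and duration, so at least 2. Paternal age is 1. Semen parameters are plural, so at least 2. That is at least 8 covariates, and 9 slopes with group.

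**3. Cycles with a euploid blastocyst.** With oocytes split evenly, the expected number of euploid blastocysts per cycle is 5.45/2 × (0.10 + 0.17) = 0.736. If the yield is Poisson, P(at least one) = 1 − exp(−0.736) = 0.521, so 0.521 × 150 ≈ 78 cycles. A more dispersed yield gives about 73, a less dispersed one about 80. With both arms at 10%, 1 − exp(−0.545) = 0.420, so 63 cycles, or about 60 with more dispersion. Counting one cycle for each of the 128 women gives fewer: 62–67 and 50–54.

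**4. Events (assumed rates).** The article gives no pregnancy or miscarriage rate. The assumed range is 40–60% pregnancy per woman with a transfer and 10–25% loss per pregnancy.
- Low: 60 × 0.40 × 0.10 = 2.4
- High: 80 × 0.60 × 0.25 = 12
- Per slope: 2.4/9 ≈ 0.3 to 12/9 ≈ 1.3

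**5. Behaviour of the model.** Null simulations used group plus 8 independent normal covariates without effect, about 60% of transfers from one arm, a fixed event count and 1,000 datasets per row. Separation was checked by linear programming. Rejection rates at nominal 5% are over all datasets.

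| Pregnancies | Miscarriages | No finite estimate | Likelihood ratio | Wald | Fisher, unadjusted |
|---|---|---|---|---|---|
| 25 | 3 | 92% | 12% | 0% | 0.6% |
| 30 | 4 | 65% | 21% | 0% | 2.3% |
| 25 | 5 | 56% | 21% | 0% | 2.8% |
| 47 | 5 | 21% | 19% | 0.3% | 1.8% |
| 32 | 6 | 24% | 21% | 0.2% | 2.2% |
| 39 | 6 | 17% | 19% | 0.5% | 2.6% |
| 47 | 7 | 5% | 12% | 1.6% | 3.8% |
| 39 | 8 | 5% | 15% | 2.1% | 4.4% |
| 47 | 9 | 1.3% | 11% | 5.3% | 3.7% |
| 47 | 12 | 0.2% | 9% | 5.6% | 4.1% |

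Separate runs agree: 89–91% without a finite estimate at 3 of 25, 36–37% at 5 of 35, 16–19% at 6 of 39, 5% at 8 of 39 and 0.2–0.4% at 12 of 47. Among datasets with a finite fit and 5 to 12 events, the likelihood-ratio test still rejects in about 9–12%.

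**6. Comparison: the clinical pregnancy model.** With the same 9 slopes and 25 to 47 pregnancies among 62 to 78 women, no dataset out of 2,000 per setting was separated. Wald rejected in 5.4–6.8% and the likelihood ratio in 6.0–8.0%.

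**The case against.** The best defence is that a valid analysis is already planned. Fisher's test stays below 5% in every row above, nothing in the article ranks the adjusted model over it, and the primary outcome is untouched. This stands, and it limits the harm to one secondary adjusted result. It does not make that result estimable.

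Second, the covariate list is open-ended, the count of eight is read from plurals, placing miscarriage among the pregnancy outcomes is an inference, and a separate analysis plan may settle the final set. This stands in part. The text nevertheless commits to the named covariates, and the general remainder clause can only lengthen the list. Even with 4 covariates, 6 events leave 5–7% of datasets without a finite estimate and a likelihood-ratio rejection rate of 9–11%.

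Three stronger readings are tempting, and the documents do not support them:
- **That the plan's own rates imply these event counts.** They fix only the number of cycles with a euploid blastocyst. The pregnancy and miscarriage rates are assumptions.
- **That the test is anti-conservative throughout.** That holds for the likelihood ratio only. Wald almost never rejects at 3 to 6 events and is close to nominal at 9 to 12, and the article names neither.
- **That the pregnancy models should be cut to maternal age alone.** Those models are estimable with slight inflation. The simulations give covariates no effect, so they cannot show any benefit of adjustment. Eligibility requires normal semen ("Male partner eligibility is not restricted beyond a requirement for normal semen analysis"), which narrows the range of the semen covariates, but how little they then explain cannot be judged from the article.

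**Conclusion.** The concern holds for the miscarriage model. Under the assumed rates it has roughly 0.3 to 1.3 events per slope. At about 6 or fewer miscarriages it fails to give a finite estimate in a substantial share of trials: about one in six at best, about nine in ten at worst. At 7 or 8 failure is about 5%, and at 9 to 12 it is under 2%, so the model is not doomed across the whole range. With few events neither usual test holds 5%, and they err in opposite directions. The size depends on the assumed 40–60% pregnancy and 10–25% loss, on at least eight covariates, and on covariates that are independent and without effect. The point is worth correcting, but it affects a secondary outcome only.

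**What to change.** In the statistical methods section {20a}, take miscarriage out of the list of outcomes for multivariable logistic regression. State instead that miscarriages will be reported as counts over clinical pregnancies in each group, with exact confidence intervals, beside the Fisher test already planned. Leave the models for the other pregnancy outcomes as they are.

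The cost is that no covariate-adjusted miscarriage estimate will be reported. No data or sample size changes. Because this changes an analysis method, the article's own amendment section {25} would, if the change is judged important, call for ethics committee approval before use and an updated registration record. The change should be dated and made before miscarriages are tabulated by group.
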